### 2.3 Morphology Classification–Guided M-TEER Procedure and Strategy 
for Commissural DMR

In this study, the morphology classification of commissural DMR and the 
corresponding classification-guided M-TEER strategy will be determined according 
to the following steps (Fig. 3). First, determine whether the mitral regurgitant 
jet originates from the commissural region. If no commissural regurgitant jet is 
present, the lesion is classified as Type I (pseudo-commissural prolapse). For 
Type I patients, a restrictive clipping strategy is planned, aiming to clip the 
true prolapsed lesion adjacent to the involved commissural area while restricting 
excessive motion of the commissural leaflet. If a commissural regurgitant jet is 
present, further assess whether degenerative mitral valve lesions are also 
present in regions other than the commissure. Patients with additional 
degenerative lesions outside the commissural region are classified as Type II 
(combined commissural prolapse), whereas those without are classified as Type III 
(isolated commissural prolapse). For Type II and Type III patients, the next step 
is to evaluate leaflet length and commissural space to determine whether the 
three coaptation lines—A-(C)-P—can be grasped simultaneously. If simultaneous 
grasping is feasible, the simultaneous clipping strategy is applied, clipping the 
A-(C)-P leaflets together in a single grasp. If, after release of the first clip, 
significant residual regurgitation persists, additional clips may be implanted to 
treat the remaining diseased A-(C)-P leaflet segments, forming a zipping clipping 
strategy. If simultaneous grasping of the A-(C)-P coaptation lines is not 
possible, a staged clipping strategy is recommended, completing repair of the 
three coaptation lines in two steps: the first clip is used to grasp the A-C or 
P-C segments to create a unified tissue bridge, followed by implantation of an 
additional clip to perform edge-to-edge repair with the adjacent P or A leaflet. 
The schematic illustration of the procedural strategy is provided in 
**Supplementary Fig. 1**.

**Fig. 3. S2.F3:**
[figure not shown]
**Flowchart of the novel morphology classification-guided M-TEER 
strategy for commissural degenerative mitral regurgitation**. A, anterior leaflet; 
C, commissure leaflet; DMR, degenerative mitral regurgitation; M-TEER, mitral 
transcatheter edge-to-edge repair; MV, mitral valve; P, posterior leaflet; TEE, 
transesophageal echocardiography; TEER, transcatheter edge-to-edge repair; TTE, 
transthoracic echocardiography; MR, mitral regurgitation; TEER-CD, Mitral Valve 
Transcatheter Edge-to-Edge Repair for Patients with Commissural Degenerative 
Mitral Regurgitation.

The M-TEER procedure was performed under general anesthesia with strict 
adherence to ultrasound-guided vascular access, using integrated fluoroscopic, 
2D, and 3D-TEE guidance. After induction of anesthesia, a guidewire and catheter 
were advanced via the femoral vein under ultrasound guidance. The device was 
delivered through a transeptal puncture, entering the left ventricle via the 
mitral valve. Optimal transeptal puncture height was targeted at 3.5–4.0  cm for 
AC pathology and 4.0–4.5  cm for PC pathology. Device positioning and deployment 
aimed to grasp and approximate the mitral leaflets, thereby reducing 
regurgitation. Continuous 2D and 3D-TEE monitoring was essential for guiding clip 
placement, ensuring perpendicular alignment to the coaptation line, and 
confirming reduction of regurgitation after clip deployment. A 3D enface view of 
the mitral valve was used to verify device orientation, and adjustments were made 
in real time based on imaging feedback to optimize procedural outcomes. Each 
participating center is encouraged to review the morphological classification for 
each patient and determine the optimal M-TEER strategy, taking into account 
patientspecific anatomy and the center’s procedural expertise.

### 2.4 Device Description

In this study, we will employ the MitraClip G3 or G4 System (Abbott, Abbott 
Park, IL, USA), a state-of-the-art transcatheter device for the treatment of 
significant symptomatic MR 3+ or 4+ grade. This system provides a nuanced 
selection of clip sizes, meticulously tailored to accommodate diverse patient 
anatomies. Specifically, the NT (normal length, standard (thin) width) and XT 
(extended length, standard width) clips feature a compact design with a 
traditional width of 4 mm and lengths of 9 mm and 12 mm, respectively. The NTW 
(normal length, wide width) and XTW (extended length, wide width) clips are 
engineered for broader anatomical needs, with dimensions of 6 mm in width and 
lengths of 9 mm and 12 mm, respectively. These dimensions facilitate a high 
degree of procedural customization essential for effective mitral valve repair. 
Each clip is designed for independent leaflet grasping and is compatible with 
left atrial pressure monitoring, features that significantly enhance the 
precision and adaptability of M-TEER for commissural DMR.

### 2.5 Patient Population

Eligible patients have symptomatic (i.e., New York Heart Association [NYHA] 
functional classification II/III/IV), or asymptomatic heart failure (HF) with 
left ventricular end-systolic diameter >40 mm; have moderate-to-severe (3+) or 
severe (4+) commissural DMR as confirmed by the study ECL prior to enrollment; 
and MR can be reduced to mild or less with the MitraClip device. A complete list 
of the TEER-CD trial inclusion and exclusion criteria appears in Table 1.

**Table 1. S2.T1:** **Inclusion and exclusion criteria**.

Inclusion criteria (all must be present)
∙ Age ≥18 years old
∙ Moderate-to-severe (3+) or severe (4+) commissural DMR, as determined by an independent ECL using standardized echocardiographic assessments (multiple etiologies are acceptable, but the main mechanism of mitral regurgitation must be degenerative)
∙ Symptomatic HF consistent with NYHA functional class II, III, or IV, or be asymptomatic but with evidence of cardiac dysfunction, such as LVESD ≥40 mm
∙ The presence of atrial septum and mitral valve anatomy that are amenable to percutaneous edge-to-edge repair as confirmed by the ECL and multidisciplinary heart team
∙ Comply with all provisions of this clinical trial and to participate in all necessary postprocedural follow-ups, and to provide a written informed consent form
Exclusion criteria (all must be absent)
∙ DMR not involving the commissural regions will be excluded to focus on the specific anatomical subset addressed by this study
∙ Presence of moderate or greater FMR [defined as central MR of grade 2+ or higher, caused by malcoaptation of the mitral leaflets outside the degenerative commissural mitral regurgitation lesion, restrictive cardiomyopathy, hypertrophic cardiomyopathy, dilated cardiomyopathy, ischemic cardiomyopathy, and infiltrative cardiomyopathy (amyloidosis, hemochromatosis, sarcoidosis, etc.)]
∙ History of mitral valve surgery or transcatheter mitral valve intervention
∙ Concurrent other moderate-to-severe (3+) or severe (4+) valvular disease requiring surgical or transcatheter intervention
∙ Acute cerebrovascular disease within 30 days
∙ Other cardiovascular surgical or interventional treatments within 30 days, such as CABG, PCI, TAVR, transcatheter carotid stenting, etc.
∙ Severe symptomatic carotid artery stenosis (ultrasound examination showing stenosis >70%)
∙ Hemodynamic instability requiring continuous intravenous medication or mechanical circulatory support treatment
∙ Echocardiographic estimation of PASP >70 mmHg or right heart catheterization measurement of PVR >3 Wood units
∙ Symptoms, signs, or echocardiographic evidence of severe right heart failure, such as TAPSE <15 mm or peak S-wave velocity <10 cm/s
∙ Severe liver cirrhosis with esophageal varices
∙ History of heart transplantation
∙ Severe hematological disorders
∙ Intracardiac mass or thrombus diagnosed by echocardiography
∙ Contraindications or high risk for TEE
∙ Poor quality of TEE imaging
∙ Known allergy or contraindication to medical agents used during the procedure
∙ Pregnancy or intended pregnancy within 12 months
∙ Anticipated need for emergency surgery or any elective cardiac surgery for any reason within 12 months,
∙ Non-cardiac disease resulting in a life expectancy of less than 12 months

CABG, coronary artery bypass grafting; DMR, degenerative mitral regurgitation; 
ECL, echocardiographic core laboratory; FMR, functional mitral regurgitation; HF, 
heart failure; LVESD, left ventricular end-systolic diameter; MR, mitral 
regurgitation; NYHA, New York Heart Association; PASP, pulmonary artery systolic 
pressure; PCI, percutaneous coronary intervention; PVR, pulmonary vascular 
resistance; S-wave,  systolic wave; TAPSE, tricuspid annular plane systolic 
excursion; TAVR, transcatheter aortic valve replacement; TEE, transesophageal 
echocardiography.

### 2.6 Subject Screening, Enrollment, and Follow-Up

#### 2.6.1 Screening

Eligible subjects for the TEER-CD trial are identified through a rigorous 
screening process that begins with a review of medical history and current 
clinical presentation. All potential participants must be aged 18 or older and 
diagnosed with symptomatic, moderate-to-severe (3+) or severe (4+) native 
commissural DMR. The diagnosis must be confirmed by an independent ECL using 
standardized assessments prior to enrollment. Patients are screened for the 
presence of specific morphological features characteristic of commissural DMR, 
including prolapse or flail involving the mitral valve commissures.

#### 2.6.2 Enrollment

Once potential participants have been identified and have met all inclusion 
criteria, they are provided with detailed information about the study, including 
the purpose, procedures, potential risks, and benefits. Informed consent is 
obtained from each participant, ensuring they understand the study requirements 
and their rights as research subjects.

#### 2.6.3 Follow-Up

After enrollment, participants undergo a comprehensive baseline assessment, 
which includes clinical examinations, echocardiography, and quality-of-life 
assessments. Following the M-TEER procedure, participants are closely monitored 
for the primary and secondary endpoints at predefined intervals: 30 days, 6 
months, and 1 year post-procedure.

The 30-day follow-up focuses on early safety and procedural outcomes, while the 
6-month and 1-year assessments evaluate the durability of the intervention and 
long-term safety. Each follow-up visit includes a physical examination, 
echocardiographic assessment, and evaluation of quality-of-life measures. Adverse 
events are captured and reported throughout the study period (Fig. 4).

**Fig. 4. S2.F4:**
[figure not shown]
**Patient flow for screening, enrollment and follow up in the 
TEER-CD trial**. DMR,  degenerative mitral regurgitation; I/E,  inclusion and 
exclusion criteria; MR,  mitral regurgitation; TEE,  transesophageal 
echocardiography; TEER,  transcatheter edge-to-edge repair; TTE,  transthoracic 
echocardiography.

In summary, the subject screening, enrollment, and follow-up processes in the 
TEER-CD trial are designed to be comprehensive, rigorous, and 
participant-centered, ensuring that the study generates high-quality data to 
evaluate the safety and effectiveness of the novel morphological 
classification-guided M-TEER approach for commissural DMR.

-Endocarditis requiring surgery
-ECL-confirmed mitral stenosis requiring surgery
-LVAD implant
-Heart transplant
-Any device-related complication requiring nonelective cardiovascular surgery
∙ Incidence of mitral chordae tendineae entanglement during TEER

ECL,  echocardiographic core laboratory; HF,  heart failure; KCCQ ,  Kansas City 
Cardiomyopathy Questionnaire; LVAD,  left ventricular assist device; LVEDV, left 
ventricular end-diastolic volume; MR,  mitral regurgitation; MV,  mitral valve; 
NYHA,  New York Heart Association; SLDA ,  single leaflet device attachment; 
TEER, transcatheter edge-to-edge repair.

Secondary efficacy endpoints encompass both procedural and clinical outcomes. 
Procedural outcomes include technical success and device success. Clinical 
outcomes include the proportion of surviving patients with MR  ≤1+ at 
30 days and 6 months, MR  ≤2+ at 30 days, 6 months, and 12 months; the 
hierarchical composite of all-cause mortality and recurrent HF hospitalization 
within 12 months; recurrent HF hospitalization and all-cause mortality within 
12 months; change in Kansas City Cardiomyopathy Questionnaire (KCCQ) score and 
6-minute walk distance from baseline to 12 months; the proportion of patients in 
NYHA functional class I or II at 30 days, 6 months, and 12 months; and change in 
left ventricular end-diastolic volume (LVEDV) from baseline to 12 months.

Secondary safety endpoints include a composite of all-cause mortality, stroke, 
myocardial infarction, cardiac hospitalization, or nonelective cardiovascular 
surgery for device-related complications at 12 months. Additional safety 
endpoints comprise a composite at 12 months of single leaflet device attachment 
(SLDA), device embolization, endocarditis requiring surgery, ECL-confirmed mitral 
stenosis requiring surgery, left ventricular assist device (LVAD) implantation, 
heart transplantation, or any device-related complication requiring nonelective 
cardiovascular surgery. The incidence of mitral chordae tendineae entanglement 
during M-TEER will also be recorded.

### 2.8 Data Collection

Data collection is standardized across all participating centers using a 
centralized electronic data capture system. This system ensures the integrity and 
consistency of the data collected, facilitating accurate and timely analysis. All 
data are monitored by an independent data management committee, which oversees 
data quality and ensures adherence to the study protocol (**Supplementary 
Table 1**).

All required data for the trial will be collected on standardized Case Report 
Forms. All protocol-mandated echocardiograms and electrocardiograms will be sent 
to the ECL (Beijing Anzhen Hospital, China). Data management and study analyses 
will be performed by National Clinical Research Center for Cardiovascular 
Diseases (Beijing, China).

### 2.9 Statistical Considerations

#### 2.9.1 Sample Size Calculation

The primary endpoint of this study is the proportion of patients achieving a MR 
grade of ≤1+ without repeat mitral intervention at 1-year follow-up. The 
study is designed as a single-arm, objective performance goal (OPG) trial with 
the following statistical hypotheses:

*H₀: P_𝑇_
≤ P₀*

*H₁: P_𝑇_
> P₀*

where *P*_𝑇_ represents the expected primary endpoint rate in this 
study, and *P₀* denotes the target performance level derived from previous 
literature.

Based on our center’s retrospective data and relevant published studies [16], 
the expected rate of the primary endpoint (*P*_𝑇_) was set at 85%. The 
target performance level (*P₀*) was set at 75%, reflecting clinically 
acceptable outcomes reported for complex MR populations in previous trials [17].

Using a one-sided significance level (α) of 0.025, a statistical power 
(1–β) of 80%, and assuming a 10% dropout rate at 12-month follow-up, 
the required sample size was calculated to be 148 patients. The sample size 
calculation was performed using the formula for a one-sample proportion test 
against a performance goal:

$$n=\frac{{\left[Z_{1-\alpha }\cdot \sqrt{P_{0}\,\left(1-P_{0}\right)}+Z_{1-\beta }\cdot \sqrt{P_{T}\,\left(1-P_{T}\right)}\right]}^{2}}{{\left(P_{T}-P_{0}\right)}^{2}}$$

where *Z*_1-α_ = 1.96 for a onesided α of 0.025, and 
*Z*_1-β_ = 0.84 for 80% power. 

#### 2.9.2 Analysis Populations

2.9.2.1 Intention-to-Treat (ITT) PopulationThe ITT population includes all participants who provided informed consent and 
received the intervention. This population is used for the primary analysis of 
the intervention’s effectiveness, regardless of adherence to the study protocol 
or completion of the study.

2.9.2.2 Per Protocol (PP) PopulationThe PP population includes participants from the ITT population who adhered to 
the study protocol, completed all scheduled visits, and received the intervention 
as intended. This population is used for sensitivity analyses to assess the 
effectiveness of the intervention under optimal conditions.In the TEER-CD trial, the primary efficacy endpoint will be rigorously assessed 
utilizing the ITT population. This approach ensures an unbiased evaluation of the 
novel morphological classification-guided M-TEER intervention, encompassing all 
participants who underwent the intervention as per the study design. The PP 
population will serve as the basis for sensitivity analyses, designed to 
scrutinize the durability of the treatment effect within a subgroup that strictly 
adhered to the study protocol. This methodological framework facilitates a 
comprehensive assessment of the intervention’s efficacy under both optimal (PP) 
and pragmatic (ITT) conditions, thereby offering a nuanced understanding of the 
intervention’s therapeutic potential. Concurrently, the safety population, which 
includes all individuals who received the intervention and had post-procedure 
safety assessments, will be employed to evaluate the safety endpoints.

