#### 2.9.3 Statistical Analysis

Baseline characteristics, procedural data, and follow-up outcomes will be 
summarized using descriptive statistics. Continuous variables will be presented 
as means ± standard deviations (SD) if normally distributed, or as medians 
with interquartile ranges (IQR) if non-normally distributed. Categorical 
variables will be expressed as frequencies and percentages.

The primary efficacy analysis will be conducted in the ITT population using a 
one-sample proportion Z-test to evaluate whether the proportion of patients 
achieving MR ≤1+ at 12 months exceeds the prespecified OPG of 75%. A 
one-sided significance level of 0.025 will be applied to test the null hypothesis 
that the success rate is less than or equal to the OPG.

Secondary endpoints will be analyzed descriptively. Comparisons of continuous 
variables between baseline and follow-up will use paired *t*-tests or 
Wilcoxon signed-rank tests based on data distribution. Categorical variables will 
be compared using McNemar’s test or Cochran’s Q test, as appropriate. 
Time-to-event outcomes will be analyzed using Kaplan–Meier estimates, with 
median survival times and event-free rates calculated at 30 days, 6 months, and 
12 months. Log-rank tests may be applied for subgroup comparisons where relevant.

To assess long-term durability, all subjects will be followed for up to five 
years. A secondary Bayesian analysis will be performed to estimate the posterior 
probability of sustained therapeutic success (defined as MR ≤1+ without 
mitral valve replacement or reintervention). This approach enables dynamic 
updating of treatment effect estimates over time and offers further insight into 
outcomes beyond the 12-month endpoint.

Predefined subgroup analyses will be performed according to the three 
morphological subtypes to evaluate the efficacy and safety of the 
classification-guided M-TEER strategy. Due to distinct procedural approaches and 
expected small sample sizes within subgroups, a dual analytic strategy will be 
employed: exact tests will be used for small-sample inference, while Bayesian 
methods will provide probabilistic estimations with credible intervals, 
incorporating prior knowledge to enhance robustness.

Sensitivity analyses will be conducted to evaluate the stability of the primary 
outcome results. These will include analyses based on the PP 
population—excluding major protocol deviations—and scenario-based imputations 

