for missing data (e.g., worst-case and best-case assumptions). Consistency 
between the ITT and PP populations, as well as across imputation methods, will 
strengthen the reliability of trial conclusions.

All statistical analyses will be conducted using a one-sided alpha level of 
0.025. Analyses will be performed using SAS software (version 9.4; SAS Institute 
Inc., Cary, NC, USA), R software (version 4.2.1; R Foundation for Statistical 
Computing, Vienna, Austria), and SPSS software (version 24.0; IBM Corp., Armonk, 
NY, USA).

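### The per-protocol set admits only patients who completed every scheduled visit, so it excludes deaths before 12 months by construction and its agreement with ITT is weak support

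*Protocol article*

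**What the plan says.** Section 2.9.2.2 forms PP from ITT patients who adhered to "the study protocol, completed all scheduled visits, and received the intervention" as intended. On its use, the section says: "This population is used for sensitivity analyses to assess the" effectiveness of the intervention under optimal conditions. The section adds that PP will "scrutinize the durability of the treatment effect within a subgroup that strictly" followed the protocol.

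Section 2.6.3 fixes the schedule: patients are monitored "for the primary and secondary endpoints at predefined intervals: 30 days, 6" months and 1 year. Section 2.9.3 also mentions follow-up of up to five years, and the PP definition does not say at which visit the completion requirement ends.

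Section 2.9.3 describes the PP analysis more briefly, as "excluding major protocol deviations", with no visit condition. It then states that consistency "between the ITT and PP populations, as well as across imputation methods, will" make the trial's conclusions more reliable.

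The primary analysis is in ITT: patients who consented and received the intervention, whatever their adherence or completion.

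**The concern.** Completing all visits is not a matter of adherence alone. It requires survival to 12 months, so membership of PP depends on an outcome of treatment. If a death is a failure of the strategy, PP removes that failure from the denominator and leaves every success of the remaining patients in place. For deaths, the shift can only be upward.

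The condition also removes survivors with a usable primary outcome who missed the 30-day or 6-month visit. The direction of that effect is unknown, but the exclusion serves no purpose for an endpoint assessed at 12 months.

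What is at stake is the reassurance drawn from PP. A reader told that ITT and PP agree will take this as evidence that the result is robust. Agreement with a set limited to survivors and completers says little about that.

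**Working it through.** **The plan's own figure.** Inputs from section 2.9.1: P0 = 0.75, PT = 0.85, one-sided alpha 0.025, power 80%, dropout 10%.

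- n = [1.960 × √(0.75 × 0.25) + 0.8416 × √(0.85 × 0.15)]² / 0.10² = 132.07, rounded up to 133.
- 133 / 0.9 = 147.8, rounded up to 148. The stated 148 reproduces.
- With the printed rounded value 0.84 in place of 0.8416, n = 131.94, rounded up to 132, and 132 / 0.9 gives 147. The difference is rounding only.

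**Effect of the visit condition.** Assumptions, none of them stated in the article:

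- a share d of treated patients dies before 12 months, with d from 2% to 10%;
- deaths count as failures in ITT;
- PP excludes no one else.

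The number of successes is then the same in both sets and only the denominator changes:

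PP rate = S / [N(1 − d)] = ITT rate / (1 − d)

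| Assumed d | PP rate if ITT rate is 75% | PP rate if ITT rate is 85% |
|---|---|---|
| 2% | 0.75/0.98 = 76.5% | 0.85/0.98 = 86.7% |
| 5% | 0.75/0.95 = 78.9% | 0.85/0.95 = 89.5% |
| 8% | 0.75/0.92 = 81.5% | 0.85/0.92 = 92.4% |
| 10% | 0.75/0.90 = 83.3% | 0.85/0.90 = 94.4% |

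**In counts.** Take 111 successes among 148 treated patients, an ITT rate of 75.0%, exactly at the goal. The one-sample Z-test needs 122 of 148, so ITT does not pass.

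- With 7 deaths, PP is 111/141 = 78.7%. It would need 116 and does not pass.
- With 15 deaths, PP is 111/133 = 83.5%. It would need 110 and passes.

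The last case is the top of the assumed range and is an illustration, not a forecast. Under these assumptions the ratio of the PP rate to the ITT rate depends on d alone, so comparing the two sets measures mortality rather than the effect of adherence.

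**The case against.** **PP is only a sensitivity set.** The primary test is in ITT regardless of completion, and section 2.9.3 also plans worst-case and best-case imputation, which covers the unfavourable direction for missing outcomes. This stands. It limits the point to the value of the supporting analysis. It does not make the PP definition sound, because the article names ITT/PP consistency as support in its own right.

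**The size rests on assumptions.** This also stands. No mortality rate is given, and the article does not say how deaths count in ITT. The primary endpoint is worded for subjects while some secondary MR endpoints are worded for surviving patients. That suggests deaths stay in the primary denominator but does not settle it. If deaths were handled as missing in ITT, the gap would depend on the imputation rule. The 10% dropout in the sample-size calculation (about 148 − 133 = 15 patients) cannot be read as deaths or as outcome-related losses. Patients who have a reintervention or recurrent MR and attend their visits remain in PP as failures, so PP does not remove failures in general.

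**Do the two PP descriptions conflict?** A reader might infer a contradiction between sections 2.9.2.2 and 2.9.3. The text does not establish one, because the phrase in 2.9.3 may be only a shorter summary of adherence to the protocol. Using one wording in both places removes the doubt.

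**Does PP fail to isolate classification-guided treatment?** A reader might infer this from section 2.3, where each "participating center is encouraged to review the morphological classification for" each patient and to choose the strategy in light of anatomy and its own expertise. But the PP definition also requires that the intervention was received as intended, and section 2.3 sets out steps by which type and strategy will be determined. Together these can be read as requiring the intended strategy, and the detail may lie in a document not shown. The documents do not show that off-strategy patients qualify for PP.

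**Conclusion.** The concern holds in a limited form. As written, the all-visits condition excludes every patient who dies before 12 months, and also survivors who have the primary outcome but missed an interim visit. If deaths are failures in ITT and PP excludes no one else, PP overstates the ITT rate by a factor of 1/(1 − d). At an ITT rate of 75% that is 1.5 to 8.3 percentage points for an assumed d of 2% to 10%. The primary ITT test is not affected. ITT/PP consistency, which section 2.9.3 counts in favour of the conclusions, is weak evidence as long as PP is formed this way.

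**What to change.** Use one PP definition in both 2.9.2.2 and 2.9.3:

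- eligibility met, intervention received as intended, and no major protocol deviation;
- no requirement to have completed all visits, which also removes the open question of where the visit schedule ends for this purpose;
- deaths and reinterventions before 12 months kept in PP as non-successes.

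For the comparison to be interpretable, deaths need to be counted in the same way in ITT.

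The cost is one rewritten definition. The PP success rate becomes less favourable, only slightly so if mortality is low. The design, sample size and primary test do not change.

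Optional addition: because section 2.3 leaves the choice of strategy partly to the centre, report descriptively how often the strategy performed matched the one assigned by the classification. In a single-arm trial this shows how far the strategy was delivered. It cannot separate the effect of the classification from operator discretion.
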